#### Inclusion criteria

3.2.1

Participants must meet all of the following criteria to be included: (1) Age between 20 and 60 years, regardless of sex; (2) underwent upper GI endoscopy at one of the participating centers within the past 6 months, with histologically confirmed CAG, defined by glandular atrophy with or without intestinal metaplasia according to the Updated Sydney System and staged using OLGA/OLGIM when feasible; (3) presence of upper GI symptoms (e.g., epigastric discomfort, pain, bloating, belching, early satiety) is recorded; symptomatic status is not required for inclusion; (4) ability to comprehend and voluntarily complete psychological assessments (e.g., depression and anxiety scales) and multimodal vascular examinations (e.g., dorsalis pedis artery ultrasound); (5) willingness to provide written informed consent and allow the use of their clinical data and examination results for research purposes.

The age range of 20–60 years was chosen to reduce heterogeneity related to adolescent developmental status and advanced age-related vascular comorbidity, thereby improving comparability across multimodal physiological assessments in the intended outpatient screening population.

#### Exclusion criteria

3.2.2

Participants will be excluded if they meet any of the following conditions: (1) History of major psychiatric disorders (e.g., schizophrenia, bipolar disorder), or currently experiencing an acute psychotic episode; (2) Recent (within 3 months) major cardiovascular or cerebrovascular events, such as acute myocardial infarction or stroke; (3) Documented severe peripheral artery disease or major anatomical abnormalities in the lower extremity vasculature—e.g., Fontaine stage III–IV peripheral arterial occlusive disease, diabetic foot with extensive ulcers or gangrene—that would preclude reliable dorsalis pedis artery ultrasound assessment; (4) Presence of severe hepatic or renal dysfunction (e.g., significantly reduced eGFR), or malignancy with a limited life expectancy; (5) Current use of systemic corticosteroids or potent immunosuppressants that may significantly alter vascular function or psychological status; (6) Pregnancy or lactation; (7) Any other condition deemed by the investigators to interfere with study participation (e.g., inability to cooperate with examinations or follow-up).

Psychiatric specialty care and/or psychotropic medication use will not be exclusionary. Medication type, dose (standardized daily dose when feasible), and duration will be recorded and adjusted for; sensitivity analyses will exclude moderate-to-high intensity regimens.

#### Grouping strategy

3.2.3

At baseline, all enrolled participants will complete the 9-item Patient Health Questionnaire (PHQ-9) to assess the severity of depressive symptoms. Based on their total PHQ-9 scores, participants will be categorized into two groups:

(1)Screen-negative group: PHQ-9 total score < 10;(2)Screen-positive group: PHQ-9 total score ≥ 10.

In secondary analyses, depressive symptom severity may also be categorized using standard PHQ-9 severity bands (e.g., 0–4/5–9/10–14/15–19/20–27) to explore dose–response patterns; the primary grouping remains PHQ-9 < 10 vs. ≥ 10.

Rationale for grouping: PHQ-9 ≥ 10 was selected as a commonly used threshold for screening-positive, clinically relevant depressive symptom burden. In the present study, it is used as a questionnaire-defined screening outcome rather than a diagnostic criterion for depressive disorder.

The planned flow of patient screening, enrolment and multimodal assessment is summarized in Figure 1.

**FIGURE 1 F1:**
[figure not shown]
Flowchart of the multicenter study protocol. The workflow illustrates the pragmatic integration of objective vascular biomarkers (dorsalis pedis Doppler, baPWV, ABI/TBI) with routine psychological screening in gastroenterology clinics across four participating centers. Key steps: Eligibility screening → Informed consent → Multimodal data collection (questionnaires plus vascular/autonomic tests) → Cross-sectional classification of questionnaire-defined symptom burden → Routine clinical safety assessment when PHQ-9 ≥ 10 or PHQ-9 item 9 is positive. In the workflow, PHQ-9 ≥ 10 and any positive response to PHQ-9 item 9 function as combined clinical safety triggers for immediate assessment; analytically, however, the primary study outcome remains PHQ-9 ≥ 10, whereas item 9 positivity is used for safety management rather than as a co-primary endpoint.

### Multimodal data collection (study procedures)

3.3

All enrolled participants undergo a standardized multimodal evaluation protocol, comprising the following four primary domains. Adjusted covariates will include age, sex, body mass index, smoking, alcohol use, education level, marital status, hypertension, diabetes, dyslipidemia, Helicobacter pylori status, medication use, and OLGA/OLGIM stage.

#### Gastrointestinal indicators

3.3.1

GI-related data include both objective findings (endoscopy and histopathology) and subjective symptom assessments.

##### Endoscopic and histological grading

3.3.1.1

Gastric mucosal features such as inflammation, atrophy, and intestinal metaplasia are recorded according to the hospital’s standardized endoscopic and pathological diagnostic procedures. Histological grading follows the Updated Sydney System, with further staging using the OLGA/OLGIM systems when feasible, to quantify gastritis severity as ordinal categorical variables.

##### GI symptom scoring

3.3.1.2

GI symptom severity is assessed using the Gastrointestinal Symptom Rating Scale (GSRS, 15 items, seven-point Likert), generating a total score and subdomain scores (e.g., abdominal pain, reflux, indigestion, diarrhea, constipation). GSRS will serve as the primary GI symptom measure for all analyses. Higher scores indicate worse symptoms.

##### *Helicobacter pylori* status and eradication history

3.3.1.3

*H. pylori* status is obtained from routine clinical records within the same endoscopy episode or within 6 months, prioritizing histology and/or rapid urease test when available; alternatively, 13C/14C urea breath test or stool antigen tests will be accepted if performed in routine care. Status will be coded as positive/negative/unknown. Prior *H. pylori* eradication therapy (yes/no, approximate timing) is recorded where feasible and considered in adjustment/sensitivity analyses.

Given that histopathological changes such as atrophy and metaplasia progress slowly, prior studies suggest OLGA/OLGIM staging is relatively stable over a 6-month window. Thus, endoscopy/pathology performed within 6 months will be considered a valid “slow-varying” proxy of current gastric mucosal status. The interval between endoscopy/histopathology and multimodal assessment will be recorded as a continuous timing variable. In addition to a sensitivity analysis restricted to participants with an interval of ≤3 months, we will explore whether this interval materially influences association estimates.

#### Peripheral vascular ultrasound and arterial stiffness metrics

3.3.2

Peripheral vascular status is assessed via dorsalis pedis artery ultrasound and standard arterial stiffness parameters.

##### Dorsalis pedis artery ultrasound

3.3.2.1

Doppler angle correction (e.g., ≤60°) and sample volume placement are standardized across participants; at least three cardiac cycles are averaged for PSV/EDV-derived indices. Using B-mode imaging, the dorsalis pedis artery is visualized between extensor hallucis longus and extensor digitorum longus tendons. Measurements include arterial diameter and anatomic trajectory. Color and pulsed Doppler modes are then used to capture the full cardiac cycle waveform and derive:

① Peak systolic velocity (PSV)

② End-diastolic velocity (EDV)

③ Resistive index (RI = (PSV–EDV)/PSV)

④ Pulsatility index (PI = (PSV–EDV)/Vmean)

⑤ Flow waveform classification (triphasic, biphasic, or monophasic)

If feasible, vessel cross-sectional area and flow volume may also be estimated. By default, the right dorsalis pedis artery is assessed. If prior vascular surgery, deformities, or measurement constraints exist, the left side is used and documented. Bilateral measurements may be obtained in some cases to allow averaging or sensitivity analyses.

Consistency will be maximized by a harmonized acquisition protocol (probe type and frequency range, Doppler angle ≤ 60°, sample volume placement, wall filter/PRF, gain, sweep speed, and averaging over ≥ 3 cardiac cycles) with site-specific standardized presets and cross-site training. Where identical equipment is not feasible, the device model, transducer, and key presets will be recorded, and site/device effects will be explored in sensitivity analyses (and/or adjusted as covariates). Sonographers will be blinded to participants’ psychological scale scores and group assignments to minimize observer bias. Doppler images and waveform recordings will be centrally archived. A blinded secondary review of a randomly selected subset is performed by the lead center to assess cross-site consistency, and site/device effects will be examined analytically as sensitivity analyses. Waveform classification (triphasic, biphasic, or monophasic) will be analyzed as an ordinal categorical variable; in the blinded secondary review subset, any classification discrepancies will be resolved by adjudication at the lead center according to the prespecified waveform criteria.

To ensure inter-center consistency, a centralized training program is conducted by the lead center (Beijing). All participating sonographers undergo standard operating procedure (SOP) training and pass a consistency evaluation (Kappa > 0.8) before study commencement.

##### Standard arterial stiffness measures

3.3.2.2

Within the same visit or within 2 weeks, participants undergo baPWV and ABI measurement using validated devices. Toe–brachial index (TBI) is also assessed when feasible. Participants must rest supine for 5–10 min prior to measurement, and procedures follow standardized device protocols and consensus guidelines to ensure reproducibility.

#### Autonomic and physiological parameters

3.3.3

This domain includes:

##### Blood pressure and heart rate

3.3.3.1

Resting seated or supine measurements are taken using an automated monitor, repeated 2–3 times with the average recorded for systolic/diastolic BP and resting HR.

##### HRV

3.3.3.2

Short-term (5-min) HRV is recorded in a quiet, appropriately lit setting using a 3-lead ECG or RR interval–capable device. Recordings will be obtained during spontaneous breathing under standardized posture (supine or seated), with participants resting quietly throughout the procedure. Respiratory rate will be documented when feasible, and residual variation related to breathing pattern will be acknowledged as a potential limitation in interpretation. Accordingly, HRV-related findings will be interpreted cautiously in view of the potential residual confounding introduced by uncontrolled respiratory variation. Device sampling specifications will also be documented. R-wave detection and artifact removal are performed using validated software, and time-domain metrics are calculated, including:

① SDNN (standard deviation of normal-to-normal intervals).

② RMSSD (root mean square of successive differences).

③ Frequency-domain analyses may also be performed if applicable.

##### Current medication use:

3.3.3.3

Information on the use of antihypertensive agents (including β-blockers), lipid-lowering agents, antiplatelet or anticoagulant drugs, and psychotropic medications (e.g., antidepressants, anxiolytics, hypnotics) prescribed in any setting (including psychiatric services) is systematically collected from medical records and patient interviews, and coded for adjustment; type, dose (standardized daily dose when feasible), and duration are recorded, and sensitivity analyses excluding moderate-to-high intensity regimens are performed.

These factors will be treated as potential sources of physiological confounding and addressed through covariate adjustment and prespecified sensitivity analyses where feasible.

#### Psychological and symptom scales

3.3.4

Validated self-report instruments are used to assess psychological burden:

##### Depression

3.3.4.1

The Patient Health Questionnaire-9 (PHQ-9) assesses depressive symptom severity over the past 2 weeks (total score: 0–27).

##### Anxiety

3.3.4.2

The Generalized Anxiety Disorder-7 (GAD-7) assesses anxiety symptoms (total score: 0–21).

##### Sleep quality

3.3.4.3

The Pittsburgh Sleep Quality Index (PSQI) assesses subjective sleep quality over the past month.

##### Health-related quality of life

3.3.4.4

Health-related quality of life is measured using the SF-12v2, yielding Physical Component Summary (PCS) and Mental Component Summary (MCS) scores.

All questionnaires are administered in a quiet environment under trained staff guidance. For participants with low literacy, items will be read neutrally and responses recorded appropriately.

Safety and referral procedures: Participants with PHQ-9 ≥ 10 or any positive response to PHQ-9 item 9 will receive prompt on-site assessment by a trained clinician, with urgent referral or emergency procedures initiated when clinically indicated.

To promote consistency in post-screen communication, clinicians will use neutral, non-diagnostic language when discussing questionnaire results and referral recommendations.

This communication approach is included as part of a standardized post-screening referral procedure for safety and consistency of clinical communication, rather than as an intervention being formally evaluated in the present study.

This strategy is intended to standardize post-screen communication across sites and reduce unnecessary variation in routine clinical explanation. Referral uptake will therefore be summarized descriptively and not interpreted as an effect of vascular findings alone.

#### Timing and reproducibility assessments

3.3.5

To minimize timing-related confounders, most assessments are performed during the same clinical episode. Endoscopy/histopathology must be within 6 months; other measures (ultrasound, baPWV/ABI/TBI, HRV, questionnaires) are completed within 2 weeks, ideally during a morning visit after an overnight fast of at least 8 h and at least 30 min without smoking, caffeine, or vigorous physical activity; when fasting is not feasible, the postprandial interval and recent caffeine/smoking will be recorded and considered in sensitivity analyses.

To assess reproducibility of dorsalis pedis ultrasound, an approximately 10% subset of participants (or at least 50 participants, depending on recruitment feasibility) undergoes repeat assessment. Intra-rater reliability is evaluated by repeat scanning after 1–2 weeks by the same sonographer, and inter-rater reliability by independent scanning by a second sonographer. Intraclass correlation coefficients (ICCs) are used for continuous Doppler indices, with ICC ≥ 0.75 prespecified as acceptable repeatability.

### Study outcomes

3.4

#### Primary outcome

3.4.1

Screening-positive depressive symptom burden, defined as PHQ-9 ≥ 10. This outcome indicates at least moderate questionnaire-defined depressive symptom burden and is intended to support further clinical assessment rather than establish a diagnosis of depressive disorder.

No structured psychiatric interview or clinician-confirmed diagnostic reference standard is incorporated into the present protocol; accordingly, the primary outcome is a questionnaire-defined screening construct.

#### Secondary outcomes

3.4.2

① PHQ-9 total score as a continuous variable (gradient of depression severity);

② GAD-7 total score (anxiety severity);

③ PSQI total and subscale scores (subjective sleep quality);

④ Descriptive workflow indicators: To characterize selected practical aspects of the assessment process in routine gastroenterology settings, we summarize:

Screening completion rate: The proportion of eligible patients who consent to and complete the vascular and psychological assessment.

Referral uptake: The proportion of screen-positive patients (PHQ-9 ≥ 10) who complete a mental health consultation within 4 weeks, as verified by medical records.

Time burden: The median time added to the routine gastroenterology workflow per patient.

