### Participants

3.2

Eligible participants will be patients diagnosed with chronic atrophic gastritis (CAG) confirmed by histopathology following upper gastrointestinal endoscopy at one of the participating hospitals. All subjects will be screened and registered according to standardized criteria.

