#### Descriptive statistics

3.5.1

Statistical analyses are prespecified using standard software (e.g., SPSS, R, or Stata). Continuous variables are expressed as mean ± SD or median (IQR), depending on distribution. The clinic-based prevalence of PHQ-9 ≥ 10 is estimated with 95% confidence intervals. We also summarize selected workflow-related indicators, including completion rates of questionnaires and vascular measurements and the proportion of screen-positive participants who complete referral when indicated. These measures are summarized descriptively [proportions with 95% CIs; time burden as median (IQR)] without hypothesis testing.

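### Two descriptive workflow indicators are loosely fixed: the completion rate's denominator is circular if read literally, and referral uptake counts visits in existing mental health care

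*Protocol article*

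**What the plan says.** **Completion rate.** Section 3.4.2 of the protocol article lists it among the descriptive workflow indicators and defines it as "The proportion of eligible patients who consent to and complete the vascular and psychological assessment". The only itemised account of eligibility is in 3.2.1, which opens with "Participants must meet all of the following criteria to be included". Criterion 5 in that list is "willingness to provide written informed consent and allow the use of their clinical data and examination results for research purposes".

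Other places suggest that eligibility is settled before consent. Figure 1 gives the order "Eligibility screening → Informed consent → Multimodal data collection", section 3.1 lists screening ahead of consent, and section 3.2 introduces the population by diagnosis alone: "Eligible participants will be patients diagnosed with chronic atrophic gastritis (CAG) confirmed by histopathology".

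**Referral uptake.** Section 3.4.2 takes patients with PHQ-9 ≥ 10 as the denominator. The numerator is those with a mental health consultation completed within 4 weeks, checked against medical records. Section 3.5.1 describes the same indicator as "the proportion of screen-positive participants who complete referral when indicated". Section 3.2.2 states that being under psychiatric specialty care, or taking psychotropic medication, does not exclude a patient.

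Section 3.5.1 reports proportions with 95% confidence intervals and no tests. Objective 4 says that the indicators are meant to inform later practice-oriented and validation research.

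**The concern.** A rate that combines consent with completion is useful only if refusers are in its denominator. If willingness to consent is a condition of eligibility, a refuser is not eligible, and the consent part of the rate is met by definition. The study's rationale is that some gastroenterology patients are reluctant to discuss mood, so refusers are the group that says most about acceptability. With several centres, each could log a refusal as ineligible or as eligible but not consenting, and the pooled rate would then mix two definitions.

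Referral uptake has a fault that does not depend on consent. The numerator does not require the consultation to follow from the study's screening. A patient already seeing a psychiatrist who attends a routine appointment within 4 weeks is scored as having taken up a referral.

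At stake are two reported secondary figures and what later studies plan from them. The primary outcome, the regression models and the sample size do not depend on either.

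**Working it through.** The document gives no expected completion or uptake rate, so there is no figure to reproduce.

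**1. Completion rate**

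Let *c* be the share of otherwise eligible patients who consent, and *k* the share of consenters who complete. Neither is in the document. The assumed ranges are *c* = 0.5 to 1.0 and *k* = 0.80 to 0.95.

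- Denominator set before consent: rate = *c* × *k*
- Denominator restricted to the willing (criterion 5 applied literally): rate = *k*
- Gap = *k*(1 − *c*); ratio = 1/*c*

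At *k* = 0.90:

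| *c* | before consent, *c* × *k* | willing only, *k* | gap (points) | ratio |
|---|---|---|---|---|
| 1.0 | 90% | 90% | 0 | 1.00 |
| 0.9 | 81% | 90% | 9 | 1.11 |
| 0.7 | 63% | 90% | 27 | 1.43 |
| 0.5 | 45% | 90% | 45 | 2.00 |

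Over *k* = 0.80 to 0.95 the gap is 8 to 9.5 points at *c* = 0.9, 24 to 28.5 at *c* = 0.7, and 40 to 47.5 at *c* = 0.5.

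With the planned enrolment of 450–520 (section 3.6), the number of refusers is *N*/*c* − *N*, with *N*/*c* rounded up:

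- *c* = 0.9: 500 − 450 = 50 to 578 − 520 = 58
- *c* = 0.7: 643 − 450 = 193 to 743 − 520 = 223
- *c* = 0.5: 900 − 450 = 450 to 1040 − 520 = 520

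On the literal reading these patients disappear from the rate. On the workflow reading they stay in and nothing is inflated.

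**2. Referral uptake**

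Three statements, side by side:

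- 3.4.2: the denominator is all screen-positive patients; the numerator is any mental health consultation within 4 weeks.
- 3.2.2: patients already under psychiatric care may be enrolled.
- 3.5.1: the proportion is of screen-positive participants, but with a qualifier about referral being indicated that 3.4.2 lacks.

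Let *e* be the share of screen-positives already in care, *v* the share of these with a visit within 4 weeks, and *u* the uptake among the rest. The reported rate is (1 − *e*)*u* + *e* *v*. It differs from *u*, the quantity of interest, by *e*(*v* − *u*). The rate is too high when existing patients attend more often than newly referred ones, and too low in the opposite case. The document gives none of the three values.

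The weight of one such patient can be bounded. The document gives prevalences of 25% (3.6) and about 15%–25% (3.7). The number of screen-positives then lies between 0.15 × 450 = 67.5 and 0.25 × 520 = 130. Each routine visit counted as uptake adds between 1/130 = 0.8 and 1/67.5 = 1.5 percentage points.

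**The case against.** **On the completion rate**, a reader might infer that the figure is inflated by construction. The document does not support that. The definition speaks of eligible patients who consent, which would be redundant if eligibility already contained consent. Figure 1 and section 3.1 both place screening before consent. The more natural intention is a denominator that keeps refusers. What remains is that the only itemised eligibility list says otherwise and nothing reconciles the two.

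A reader might also infer that criterion 4, "ability to comprehend and voluntarily complete psychological assessments", or the exclusion for "inability to cooperate with examinations or follow-up", removes non-completers and drives the rate towards 100%. Both concern ability, not actual completion. Someone who consents and does not finish stays in the denominator on either reading, so only refusal can be lost.

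**On referral uptake**, a reader might infer that 3.4.2 and 3.5.1 use two denominators. On assumed counts of 115 screen-positive, 60 referred and 30 attending, that would give 30/115 = 26% or 30/60 = 50%. But both sections count among screen-positive participants, and neither states a referred-only denominator. The qualifier in 3.5.1 needs aligning; it does not establish a second rate. Moving to referred patients only would be a different estimand and a matter of preference.

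The article does caution (3.3.4.4 and 5.5) that uptake cannot be attributed to the vascular findings alone. That stands, but it does not meet the point: 5.5 treats uptake as the result of screening and communication together, whereas a routine visit in existing care need owe nothing to either. Section 3.3.3.3 records psychotropic medication, including from psychiatric services. That would identify some of these patients, but the uptake definition makes no use of it.

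It is also fair that the indicators are descriptive and untested, and that screening-log detail commonly sits in a fuller document. The point here is the definitions that the article does state, not the absence of a log.

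**Conclusion.** Both definitions need tightening. The completion rate has an unreconciled denominator: circular under criterion 5 read literally, sound under the workflow reading. Any inflation ranges from none to a factor of 1/*c*, and *c* is not in the document, so the percentages above illustrate the dependence and do not estimate a bias. The uptake fault lies in the stated rule itself: existing-care visits qualify as uptake. Its net size and direction depend on quantities the document does not give, at roughly 0.8 to 1.5 points per visit so counted. The consequences are confined to two descriptive secondary figures.

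**What to change.** **Completion rate (3.4.2).** State that the denominator is all consecutive patients who meet the clinical and histological criteria before consent is sought, with criterion 5 set aside for this purpose. Record a patient who declines as a refusal, not as ineligible. Report the consent rate and completion among consenters separately; their product is the overall rate.

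**Referral uptake (3.4.2 and 3.5.1).** Keep the screen-positive denominator of 3.4.2 and reword 3.5.1 to match. Report the number referred alongside it. Record at baseline whether the patient is already in mental health care, and exclude these patients from the indicator or count them separately.

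**Cost.** Two reworded definitions, a count of refusals at each site and one baseline item. The article says that nobody has been enrolled, so this can be in place from the first patient; refusals not counted at the time may be impossible to recover later. The reported rates may come out lower. The primary analysis and the sample size do not change.

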### Limitations and conclusion

5.5

Several inherent limitations should be acknowledged. First, the proposed design is a multicenter, cross-sectional observational study conducted at specialist hospitals in northern China, which—even with adequate sample size—limits the ability to infer temporal or causal relationships between gastritis severity, vascular dysfunction, and depression onset. Observed associations should be interpreted as co-occurring patterns or cross-sectional correlates, not mechanistic pathways. Consistent with this cross-sectional design, all uses of terms such as “screening,” “risk stratification,” or “prediction” in this protocol refer to the cross-sectional identification of patients with higher concurrent depressive symptom burden, rather than forecasting future onset of depression. Although cross-sectional data cannot establish temporal direction or causality, they are appropriate for the present study’s aims of phenotype characterization, association analysis, and concurrent identification of questionnaire-defined symptom burden within a defined clinical population. Any future referral-related application would require more than a cross-sectional statistical association and should be evaluated only after external validation and clearer clinical reference standards. Referral uptake reflects the combined screening-and-communication process and cannot be attributed solely to the vascular findings themselves.

Second, the dorsalis pedis artery is only one of many assessable peripheral arteries; whether its hemodynamic alterations accurately reflect systemic microvascular status remains uncertain. Future studies should integrate retinal and cerebral microvascular imaging for triangulation.

Third, although this is a multicenter study, all participating hospitals are specialist centers located in northern and eastern China, which implies potential limitations in generalizability, related to patient characteristics, workflow, and equipment availability, and external validation in diverse healthcare settings will be necessary. In addition, cultural factors related to stigma, symptom reporting, and willingness to accept mental health referral may differ across settings, which may further limit direct extrapolation to other populations and healthcare systems.

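### As defined, referral uptake can count a continuing psychiatric visit as uptake of the study referral, and the article words the indicator in two ways that do not match

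*Protocol article*

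**What the plan says.** All references are to the protocol article.

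- **Section 3.4.2 (Secondary outcomes)** lists referral uptake among the descriptive workflow indicators and defines it as "The proportion of screen-positive patients (PHQ-9 ≥ 10) who complete a mental health consultation within 4 weeks, as verified by medical records". This fixes the denominator, the event, the time window and the source of verification.
- **Section 3.2.2 (Exclusion criteria)** excludes "History of major psychiatric disorders (e.g., schizophrenia, bipolar disorder), or currently experiencing an acute psychotic episode", but also states: "Psychiatric specialty care and/or psychotropic medication use will not be exclusionary".
- **Section 3.3.3.3 (Current medication use)** says that information on "psychotropic medications (e.g., antidepressants, anxiolytics, hypnotics) prescribed in any setting (including psychiatric services) is systematically collected". Its stated use is covariate adjustment and sensitivity analyses.
- **Section 3.5.1 (Descriptive statistics)** gives a second wording, "the proportion of screen-positive participants who complete referral when indicated", and the analysis: "These measures are summarized descriptively [proportions with 95% CIs; time burden as median (IQR)] without hypothesis testing".
- **Section 3.3.4.4**, in its text on safety and referral procedures, adds: "Referral uptake will therefore be summarized descriptively and not interpreted as an effect of vascular findings alone".
- **Section 5.5 (Limitations and conclusion)** interprets the result: "Referral uptake reflects the combined screening-and-communication process and cannot be attributed solely to the vascular findings themselves".

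**The concern.** A participant treated for depression by a psychiatric service is eligible and may score 10 or more on the PHQ-9. If that participant keeps a routine appointment within the next 4 weeks, every element of the section 3.4.2 definition is met, although no study referral was taken up. Checking the medical record confirms that a visit took place, not why.

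The indicator's name and its interpretation in section 5.5 both tie it to what screening and the conversation afterwards achieved. Continuing-care visits would have happened without either. Objective 4 (section 2) wants the workflow indicators to inform later practice-oriented research, so a later study might plan around a figure that mixes new linkage with existing care. The planned confidence interval would not reveal this, because it reflects sampling error only.

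**Working it through.** **1. The two wordings side by side.** Section 3.4.2 takes all screen-positives as the denominator and a completed mental health consultation as the event. Section 3.5.1 makes the event the completion of a referral, and only where one is indicated. A screen-positive participant already in care who attends a booked visit counts under section 3.4.2. Under section 3.5.1, the same participant might not count, or might leave the calculation altogether; the text does not say. The wordings therefore differ in the event and possibly in the denominator.

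**2. Size of the denominator.** The article gives no expected value for uptake. The only relevant design figure is the enrolment target in section 3.6, which reproduces closely:

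- 10 events per variable × 10 to 12 variables = 100 to 120 events.
- 100/0.25 = 400 and 120/0.25 = 480 participants.
- Allowing for 10% missing: 400/0.90 ≈ 445 and 480/0.90 ≈ 534, against the stated 450–520.

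At 25% prevalence, the screen-positives number 0.25 × 450 = 112.5 to 0.25 × 520 = 130. At 15%, the lower end of the range in section 3.7, they number 67.5 to 78.

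**3. Bias formula.** Three inputs are needed, and the documents give none of them:

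- *u*: true uptake among screen-positives not in care.
- *f*: share of screen-positives already in care.
- *c*: probability that a participant already in care has a visit within 4 weeks.

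Reported uptake = *f·c* + (1 − *f*)·*u*, so the bias is *f*·(*c* − *u*). It is upward whenever *c* exceeds *u*.

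**4. Results with *u* = 30% (assumed).**

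| *f* | Reported, *c* = 50% | Reported, *c* = 80% | Overstatement (points) |
|---|---|---|---|
| 5% | 31% | 32.5% | 1 to 2.5 |
| 10% | 32% | 35% | 2 to 5 |
| 20% | 34% | 40% | 4 to 10 |
| 30% | 36% | 45% | 6 to 15 |

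Worked cell: *f* = 20%, *c* = 80% gives 0.20 × 0.80 + 0.80 × 0.30 = 0.16 + 0.24 = 0.40. Of the counted uptakes, 0.16/0.40 = 40% are continuing care.

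Letting *u* run from 20% to 40% widens the overstatement to between 0.05 × (0.50 − 0.40) = 0.5 points and 0.30 × (0.80 − 0.20) = 18 points.

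**5. Comparison with sampling error.** For a 30% proportion the 95% half-width is 1.96 × √(0.30 × 0.70/112) = 8.5 points and 1.96 × √(0.30 × 0.70/130) = 7.9 points. With *c* = 80%, the bias passes 8 points once *f* exceeds 0.08/0.50 = 16%. With *c* = 50%, it does so only once *f* exceeds 0.08/0.20 = 40%. At *f* of 5% or 10% it stays inside the half-width throughout the table.

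**6. Precision after the fix.** If *f* = 20%, the denominator falls to 0.80 × 112.5 = 90 or 0.80 × 130 = 104. The half-widths become 1.96 × √(0.21/90) = 9.5 and 1.96 × √(0.21/104) = 8.8 points, a loss of about one point.

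**The case against.** **The indicator's name and the section 3.5.1 wording point to a visit that follows a referral.** This is the best defence. Read with the referral procedure in section 3.3.4.4, they suggest that the intended event is a consultation resulting from the study referral. It would go too far to infer that the plan sets out to count continuing care, or certainly will. What remains is that the fullest definition, in section 3.4.2, does not carry the condition, and that section 3.5.1 neither excludes existing care nor uses the same denominator.

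**The size is assumed.** This stands. A reader might infer that treated patients are over-represented among screen-positives, that their share differs between centres, or that the bias must exceed the confidence interval. The documents support none of these. The introduction describes patients whose depressive symptoms may go unrecognised, which is compatible with a low share in care and a bias of 1 to 2.5 points.

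**The indicator carries little weight.** This also stands. It is descriptive and untested, and section 5.4 leaves formal assessment of referral outcomes to later studies.

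**The caveats already cover it.** They do not. Sections 3.3.4.4 and 5.5 warn against attributing uptake to the vascular findings; neither mentions care that was already under way.

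**Operational detail belongs in the full protocol, and prescriptions are already collected.** Partly true. How a visit is coded can be left to other documents, but the article does state a complete definition, and that definition admits the wrong event. Prescription data would allow a partial split, but would miss participants in psychiatric care without medication, whom section 3.2.2 also admits through its and/or wording.

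**Linkage to care among all screen-positives is a legitimate measure.** It is, but then it should carry that name and not be read as the product of screening and communication.

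**Conclusion.** The point holds as a minor one. By the definition in section 3.4.2, a continuing-care visit unrelated to the study referral counts as referral uptake, and section 3.5.1 describes the indicator in terms that do not match. The reported figure can therefore overstate what section 5.5 says it reflects.

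The documents do not allow the overstatement to be estimated. About 1 to 15 points follows only from assuming 30% true uptake, 5–30% of screen-positives already in care and 50–80% of those seen within 4 weeks. It also requires that participants in care are seen more often within 4 weeks than newly referred participants take up the referral; if not, the bias vanishes or reverses. The association models, the primary outcome and the sample size are untouched.

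**What to change.** - Add a baseline yes/no field for current mental health care, separate from the medication record.
- Define referral uptake as a mental health consultation within 4 weeks that follows the study referral, among screen-positive participants not currently in care. Do not limit it to a first-ever consultation: that could drop people with lapsed care whom the referral brings back.
- Show screen-positives already in care in a separate row, with the proportion seen within 4 weeks.
- Use one wording in sections 3.4.2 and 3.5.1, and state whether screen-positives for whom no referral is indicated stay in the denominator.

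The cost is one data field, one definition sentence and one table row, plus a smaller denominator and a slightly wider interval. The article reports that nobody had been enrolled at submission, so if that is still so the field can be in place from the first participant. The change concerns only how the indicator is counted; the safety and referral procedures are unaffected.
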